### Statistical analysis

We will use SPSS 23.0 statistical software for Windows to perform statistical analysis. To ensure the reliability of our conclusions, we plan to use intention-to-treat (ITT) analysis as the primary form of research.

### Baseline description

Means ± standard deviations (SD) will be used to describe normally distributed quantitative data; medians and interquartile ranges (IQRs) will be used to describe nonnormal distribution data. Blood lipid, hs-CRP, homocysteine, liver function, and kidney function data will be determined if it is normally distributed or not to decide whether to use SDs or IQRs. The constituent ratio or relative ratio will be used to describe the count data (recovery of the carotid canal cavity and plaque clearance).

### Comparison of baseline data

*T*-tests will be performed for quantitative data that are usually distributed, and a nonparametric test will be used for quantitative data that are not normally distributed, including blood lipids, hs-CRP, homocysteine, liver function, and kidney function. The chi-squared (*χ*^2^) test will be used for counting data, including recovery of the carotid canal cavity and plaque clearance. A two-sided *P*-value < 0.05 will be considered statistically significant.

### Interim analysis

During the randomized controlled trial (RCT), one safety check will be performed when 50% of the needed patients are enrolled and the 3-year follow-up has been completed for these patients. The data will be shared by the program coordinator with the DMC, who will perform the interim analysis. The DMC is not involved in the direct implementation of the treatment. If a statistically significant difference is observed and the carotid restenosis rate in the experimental group is higher than that in the control group, the trial will be ended; otherwise, the trial will be kept secret from the researcher and continue as planned in both groups.

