## Methods/design

### Study design

This prospective, randomized, double-blind, single-center, superiority clinical trial will be conducted at the Second Affiliated Hospital of Chongqing Medical University in China. The study was registered with the Chinese Clinical Trial Registry on 18 July 2023 (ChiCTR2300073652). The plan is to recruit 276 eligible subjects and assign them to either the control group (standard CEA therapy) or the experimental group (CEA+ carotid sinus nerve transection, CSNT) at a 1:1 ratio. Participants will be hospitalized for 2 weeks and will have a 3-year follow-up period. The trial flow chart is shown in Fig. 1.

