### Recruitment and eligibility criteria

Enrollment will be completed within 3 years (from the beginning of recruitment to the last patient). Enrollment is projected to begin on July 18, 2023. Recruitment advertisements for the study will be placed on the WeChat public website and hospital websites. The research staff ([name], [name], [name], [name], and [name]) will screen inpatients and outpatients according to the inclusion and exclusion criteria.

The inclusion criteria are as follows: (1) aged 55–80 years, female or male; (2) symptomatic carotid artery stenosis and noninvasive examination showed that the stenosis of the carotid artery was ≥ 70%, or angiography showed that the stenosis exceeded 50%; (3) internal carotid artery was not completely occluded; (4) National Institutes of Health Stroke Scale (NIHSS) scores ≤ 4; and (5) the patient and his or her family members were informed and provided signed and informed consent before surgical treatment. The exclusion criteria are as follows: (1) CEA or CAS surgery for unilateral or bilateral; (2) clinical status complicated by severe organ system diseases such as renal failure, heart failure, and liver cirrhosis; (3) serious psychological disease; and (4) severe arrhythmia or carotid sinus syndrome.

The withdrawal criteria are as follows: (1) voluntary withdrawal during the intervention, (2) alcohol and/or drug abuse, and (3) any other reasons considered inappropriate by the investigators.

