### Surgical treatment

All patients will be treated with a CEA standard operation. After general anesthesia, the patient will be placed in the supine position, with the shoulder pad, head and neck facing the contralateral hyperextension position, and the basal blood pressure level will be maintained. During the operation, the changes in intracranial blood flow will be monitored by transcranial Doppler. The carotid artery and its branches will be dissected along the incision at the front edge of the sternocleidomastoid muscle. If the patient’s carotid artery bifurcation is high or the lesion area is extended, the digastric power can be cut off to block the distal end of the internal carotid artery. After dissecting the bifurcation of the common carotid artery, internal carotid artery, external carotid artery, and superior thyroid artery clearly, a blocking band will be sleeved, and appropriate blocking forceps will be selected for later use. After the preparation is finished, whole body heparin will be given at 1 mg/kg, and 1% lidocaine will be used for carotid sinus infiltration anesthesia. To avoid excessive blood pressure fluctuation, a longitudinal incision will be made to cut the blood vessel, peel off the plaque, and remove it as altogether as possible. Heparin saline will be used to wash the peeling surface, and the intimal flap will be floated to fix it. The blood vessel will be sutured, the blocking forceps will be loosened, and the blood pressure will be lowered by 10–20% of the basal blood pressure to reduce the risk of postoperative overperfusion. The subcutaneous tissue and skin will be sutured in turn. After suturing, the coagulation function will be checked urgently, and whether to use protamine to neutralize heparin will be decided according to the results.

In the experimental group, after suturing the blood vessels, the carotid sinus nerve will be searched for along the front of the internal carotid artery, separated and exposed approximately 1 cm in length to be entirely transected, and then the subcutaneous and skin will be sutured layer by layer.

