### Sample size

The determination of sample size was calculated by SPSS 23.0 software. Based on a previous study and clinical assumptions, carotid restenosis was 5–22% [4–6]. Our previous research showed that the restenosis rate of the carotid artery after CEA in our hospital was approximately 15%. The statistical parameters were set as follows: one-sided log-rank testing with 80% power, the probability of obtaining a false-positive with a statistical test at 0.05, and a 3-year follow-up time. Considering a potential dropout rate of 5% across both groups, it is estimated that 276 patients will need to be enrolled (138 participants per group).

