### Trial status

The trial started on July 18, 2023, and recruited 13 patients in our hospital. The trial was started according to the protocol in its second version dated March 23, 2023. There were minor protocol modifications after starting the trial (versions 3.0, date July 30, 2023); the only change was that the total sample size was revised to 276 patients, and this change had no impact on the study conduct. According to the planned timeframe, recruitment will be ongoing until March 31, 2024, and patient follow-up is expected to be completed by March 31, 2027. Upon completion, the results of the trial will be shared in an open-access journal. The protocol modifications will be submitted to the REC and the Chinese Clinical Trial Registration authority for review and record by website uploading.

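### The interim safety check falls after enrolment has closed on both stated timelines, so it cannot spare any patient the nerve transection, and its only trigger is the efficacy outcome

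*Protocol article*

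**What the plan says.** All references are to the protocol article.

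- **Timing of the check** (Interim analysis): "one safety check will be performed when 50% of the needed patients are enrolled and the 3-year follow-up has been completed for these patients".
- **Trigger** (same section): "If a statistically significant difference is observed and the carotid restenosis rate in the experimental group is higher than that in the control group". In that case the trial ends. Otherwise it continues, and the result is withheld from the researchers. The DMC performs the analysis.
- **Size** (Sample size): "it is estimated that 276 patients will need to be enrolled (138 participants per group").
- **Enrolment, first statement** (Recruitment and eligibility criteria): "Enrollment will be completed within 3 years (from the beginning of recruitment to the last patient").
- **Enrolment, second statement** (Trial status): "The trial started on July 18, 2023, and recruited 13 patients in our hospital"; then "recruitment will be ongoing until March 31, 2024, and patient follow-up is expected to be completed by March 31, 2027".
- **Follow-up** (Study design): "Participants will be hospitalized for 2 weeks and will have a 3-year follow-up period".
- **Exposure** (Surgical treatment): after the vessel is sutured, the carotid sinus nerve is "separated and exposed approximately 1 cm in length to be entirely transected". This is done once, in the same operation.
- **Safety outcomes** (Safety evaluation; Reports of adverse events): arrhythmia and blood pressure variability, with severe arrhythmia as the serious event.
- **Other monitoring** (Quality control): an independent DMC reviews progress, safety data and essential efficacy data yearly, and the ethics committee also reviews the trial yearly.

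**The concern.** An interim harm check in a surgical trial is useful mainly because it can stop further patients receiving a harmful procedure. It must therefore report while patients are still to be operated on. Here the check needs complete three-year follow-up of half the sample, but enrolment lasts at most three years.

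There is no continuing treatment to withdraw, so a stop at that point protects nobody from the transection. It would also lose the remaining follow-up, which is where late harm would show.

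The content is a second mismatch. The article calls this a safety check, yet the only criterion is the restenosis rate, which the Discussion names as the main index of the study. The outcomes that the article itself treats as safety outcomes have no part in it.

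**Working it through.** **Inputs.** Start 18 July 2023 (Trial status). Planned N = 276, half = 138 (Sample size). Follow-up three years (Study design). Closure of enrolment: timeline A, within three years, so by 18 July 2026 (Recruitment and eligibility criteria); timeline B, 31 March 2024 (Trial status). Uniform accrual is my assumption and is relaxed in step 3.

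**Step 1. Reproduce the article's own date.** Last enrolment + 3 years = 31 March 2024 + 3 years = 31 March 2027. This matches the stated end of follow-up.

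**Step 2. Date of the check = date of the 138th enrolment + 3 years.**

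| | Timeline A | Timeline B |
|---|---|---|
| Length of enrolment | 36 months | 257 days |
| Implied rate | 276/36 = 7.7 per month | 276/(257/30.44) = 32.7 per month |
| 138th patient (uniform) | about 16 Jan 2025 | about 23 Nov 2023 |
| Check | about 16 Jan 2028 | about 23 Nov 2026 |
| Time after closure | 547 days (18 months) | 967 days (32 months) |
| Time before last follow-up | 18 months | 4 months |
| Planned patient-years already accrued | 87% | 97% |
| Patients still to be enrolled | 0 of 276 | 0 of 276 |

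**Step 3. Dependence on accrual.** The 138th patient enters after day 0, so the check falls after month 36. Timeline A has closed by month 36. On timeline B the check cannot fall before 18 July 2026, at least 839 days after closure. Counting follow-up from surgery rather than enrolment moves the check later. The conclusion would fail only if enrolment ran on for more than three years after the 138th patient, which neither timeline allows.

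**Step 4. The yearly DMC review.** Counted from the start, the first review is about 18 July 2024. On timeline A, reviews at 12 and 24 months fall inside enrolment. On timeline B the first falls 109 days after closure (31 March to 18 July 2024).

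**Step 5. An earlier check: 50% enrolled plus the 3-month visit (uniform accrual).**

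- Timeline A: month 18 + 3 = month 21. Enrolled: 276 × 21/36 = 161. Remaining: 115.
- Timeline B: 23 Nov 2023 + 3 months = 23 Feb 2024, day 220. Enrolled: 276 × 220/257 = 236. Remaining: 40, about 20 of them in the experimental arm.
- On timeline B each further week, for the interval to surgery or for DMC review, uses up about 276 × 7/257 = 7.5 patients.

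**The case against.** The strongest reply is that the trial does not rely on this check alone. An independent DMC sees safety data yearly, the ethics committee reviews yearly, and severe adverse events go promptly to the principal investigator and the ethics committee. That stands, and a reader who inferred that nothing in the trial can protect a patient would go too far. The absence of a stated rule for the yearly review is no fault either, since an article commonly leaves such guidelines to a DMC charter. The reply is weaker on the Trial status dates, where a first review at 12 months also comes after closure.

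Three other stronger readings are tempting, and the article does not support them.

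- **The check unblinds the trial.** The data go to the DMC, and the result is kept from the researchers unless the trial ends.
- **The check inflates the false-positive rate for benefit.** It stops only for a higher restenosis rate in the experimental arm, so the superiority claim is not affected.
- **The check is shown to be underpowered.** The article gives no harmful rate. With 69 per arm, 15% restenosis in the control arm and a two-sided 0.05 level, power runs from about 12% to 78% as the assumed experimental rate runs from 20% to 35%. Any single figure is a choice, and the point does not need one.

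It can also be said that an earlier check gains little on the shorter timeline. That is fair, and it is why the fix depends on settling the timeline.

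**Conclusion.** The point holds as a matter of dates. The one formal check described falls after all 276 patients are enrolled on both stated timelines: about 32 months after closure on the Trial status dates and about 18 months on the three-year window. Those two figures assume uniform accrual; the ordering does not. Ending the trial at that point spares no patient the transection. The safety label also does not match a trigger that consists of restenosis alone.

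The primary estimate, its type I error and the sample size are unaffected, and other oversight exists. This should be fixed, but it does not undermine the trial's main result.

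**What to change.** 1. **Move the formal DMC safety check into the enrolment period**, for example to when 50% of patients are enrolled and have completed the scheduled 3-month visit.
2. **Match its content to its name.** Review by arm the adverse events already collected (arrhythmia, blood pressure) together with restenosis to date. Keep it harm-only, as now. The sponsor and the DMC should set the criterion before the look.
3. **Reconcile the two recruitment timelines.** If the shorter one holds, consider an earlier look, because about 40 patients at most would remain.
4. **If a three-year look is kept**, do not describe it as a safeguard against exposure. It need not be dropped.

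The cost is a change of wording in the protocol and the DMC documents, with the same committee and the same visits. The drawback is that few restenosis events will have occurred by the earlier look, so it will mainly inform on early adverse events.

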### Quality control

#### Composition of the coordinating center and trial steering committee

The trial will be performed by the neurosurgery of the Second Affiliated Hospital of Chongqing Medical University. There is no other coordinating center. The trial steering committee consists of the ethics committee of the Second Affiliated Hospital of Chongqing Medical University (ID: LKSD-2023-88) and the clinical research team. The research team consists of three principal investigators who oversee the study and are responsible for medical responsibilities, a study coordinator who plans patient visits, and an investigator who is responsible for data management and trial management. The research team meets monthly to assess the progress, identify potential test subjects, and work out logistical issues. A statistician was involved in the design of the trial and will be consulted on statistical issues throughout the study. [name], [name], and [name] will identify the enrolled patients in the outpatient department. A researcher will collect general patient information. To improve the reliability of the test and reduce the differences between operators, the following measures will be taken: all the operations will be led by [name], and all the operations will be photographed and recorded by video. The test data will be evaluated and counted by one person.

A data monitoring committee (DMC), consisting of neurosurgery experts and statisticians, will be established, independent of the sponsor and trial investigator. The DMC will assess the progress of the clinical trials, safety data, and essential efficacy data yearly. The DMC will assess the progress of the clinical trials, safety data, and essential efficacy data yearly. The REC meeting will also assess the ethics of the trial every year.

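### The only stated stop rule waits for 3-year data on half the patients, so it cannot act until enrolment has closed and everyone has been operated on

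*Protocol article*

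**What the plan says.** All references are to the protocol article.

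- **Interim analysis:** "one safety check will be performed when 50% of the needed patients are enrolled and the 3-year follow-up has been completed for these patients". The DMC carries out the analysis. If the difference is statistically significant and "the carotid restenosis rate in the experimental group is higher than that in the control group, the trial will be ended"; otherwise both groups carry on as planned. No other stop rule is stated.
- **Sample size:** "it is estimated that 276 patients will need to be enrolled (138 participants per group"), so half is 138.
- **Recruitment and eligibility criteria:** "Enrollment will be completed within 3 years (from the beginning of recruitment to the last patient"), with a projected start on 18 July 2023.
- **Trial status:** the trial started on 18 July 2023, and "recruitment will be ongoing until March 31, 2024, and patient follow-up is expected to be completed by March 31, 2027".
- **Quality control, on the composition of the committees:** "The DMC will assess the progress of the clinical trials, safety data, and essential efficacy data yearly". No first date, stop rule or review by arm is given.
- **Surgical treatment:** the carotid sinus nerve is cut through completely in the experimental group, during the same operation as the endarterectomy.
- **Reports of adverse events and Randomization and blinding:** severe adverse events go promptly to the principal investigator and the ethics committee, and can trigger emergency unblinding.

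**The concern.** The experimental treatment is given once, in the operating theatre. There is no later dose to withhold. A rule that ends the trial for harm can therefore keep patients from the procedure only if it can act while some are still waiting for surgery.

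The interim look is labelled a safety check, and its consequence is to end the trial. Yet its trigger requires 3 years of follow-up on half the sample, while recruitment of the whole sample takes at most 3 years. When the rule can first act, all that is left to stop is follow-up. A reader, an ethics committee or a participant would take the label to promise a protection that this rule cannot give.

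**Working it through.** **1. Inputs.** N = 276, so half is 138 (Sample size). Start is 18 July 2023 (Trial status). Close is 31 March 2024 (Trial status) or at the latest 18 July 2026 (start plus the 3-year limit in Recruitment and eligibility criteria). Follow-up is 3 years. I assume surgery close to enrolment.

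**2. The plan's own figure.** Last enrolment 31 March 2024 + 3 years = 31 March 2027. This matches the stated end of follow-up.

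**3. Bound without any accrual assumption.** Let t138 and t276 be the enrolment times of patients 138 and 276, counted from the start.

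- Look = t138 + 3 years ≥ 3 years.
- Close = t276 ≤ 3 years.

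So the look cannot precede the close. They coincide only if 138 patients were enrolled on day 0 and enrolment also ran to the full limit. For the look to fall inside enrolment, more than 3 years would have to pass between patients 138 and 276, which the limit excludes. The earliest possible look is 18 July 2026, which is 839 days after the Trial status close.

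**4. Uniform accrual.** Look = start + half the accrual period + 3 years. Months are days ÷ 30.4375.

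| | Trial status dates | 3-year limit |
|---|---|---|
| Accrual period | 257 days | 1,096 days |
| Patient 138 enrolled | 23 Nov 2023 | 16 Jan 2025 |
| Look | 23 Nov 2026 | 16 Jan 2028 |
| Look after close | 967 days (31.8 months) | 547 days (18.0 months) |
| Last 3-year visit | 31 Mar 2027 | 18 Jul 2029 |
| Look before last visit | 128 days (4.2 months) | 549 days (18.0 months) |
| Patients left to operate on | 0 of 276 | 0 of 276 |

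**5. Yearly DMC review.** The article does not date the first review. If it is counted from trial start, it falls on 18 July 2024.

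- Trial status dates: 109 days after close, with 0 patients left.
- 3-year limit: 366/1,096 × 276 ≈ 92 operated on, so about 184 are left. A second review in July 2025 would leave about 92.

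**6. What an earlier review could reach.** Take a look when the 69th patient completes the 3-month visit, again with uniform accrual.

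- Trial status dates: patient 69 enrols at 257/4 ≈ 64 days (20 September 2023), so the look is about 20 December 2023, day 155. Operated on: 155/257 × 276 ≈ 166. Left: about 110.
- 3-year limit: the look is in mid-July 2024. Operated on: about 92. Left: about 184.

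With 138 patients as the trigger:

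- Trial status dates: about 23 February 2024, day 220. Operated on: 220/257 × 276 ≈ 236. Left: about 40.
- 3-year limit: about 16 April 2025, day 638. Operated on: 638/1,096 × 276 ≈ 161. Left: about 115.

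**The case against.** **Other planned reviews may come in time.** A reader might infer that no planned review of any kind can spare a patient the transection. The document does not support that. It gives no date for the first yearly DMC review, and a meeting before 31 March 2024 would fall during enrolment. If recruitment runs towards the 3-year limit, one or two yearly reviews fall inside it. That is plausible: 276 patients in 257 days is about 33 a month at one centre, and Trial status reports 13 recruited at an undated point. This objection stands, so the point is confined to the stop rule in Interim analysis. The DMC part is conditional on the timeline and on an assumed first date.

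**Other safeguards exist.** Prompt reporting of severe adverse events, emergency unblinding and yearly ethics review all operate during enrolment. It would be wrong to say that patients have no protection. But event reporting and unblinding work case by case, and no comparison of arms is described for any of the three, so none is set up to show an excess of events in one arm.

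**One check and yearly reviews need not conflict.** One may be a formal analysis with a stop rule and the other routine oversight. That is a fair reading; the article simply does not say how they relate.

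**A DMC charter or the full protocol may hold the detail.** This answers the missing first date, but not the interim trigger, which the article fixes itself.

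**A tempting comparison to avoid.** The January 2028 look should not be set against the March 2027 end of follow-up. The first assumes recruitment to the 3-year limit and the second assumes closure in March 2024. At the limit, follow-up would end in July 2029.

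**Conclusion.** The point holds for the interim stop rule on both timelines that the article gives. The rule can act no earlier than the close of enrolment, and under uniform accrual it acts about 32 months (Trial status dates) or about 18 months (3-year limit) after it. It can spare 0 of 276 patients. The bound itself needs no accrual assumption, only that the 3-year limit on recruitment is kept; the calendar dates assume uniform accrual from 18 July 2023.

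Whether the yearly DMC review shares the problem is open. Counted from trial start, it comes 109 days too late on the Trial status dates, but with about 184 patients still to be operated on at the 3-year limit. On either timeline the article gives it no stop rule. The conclusion concerns the timing of review, not which finding should end the trial.

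**What to change.** In Interim analysis, tie a DMC harm review by arm to the number of patients operated on while recruitment is open. For example, hold it when about 69 and 138 patients have completed the 3-month visit; these triggers are illustrative. Table 1 already schedules ultrasound, ECG and adverse events at that visit, so no new assessment or patient is needed. Make these looks harm-only, with no stopping for efficacy, so that no efficacy alpha is spent. Leave the harm criteria to the DMC.

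In Quality control, state when the first yearly DMC review takes place and how the yearly reviews relate to the single check in Interim analysis. Reconcile the two recruitment timelines so that these dates can be fixed. Stop presenting the 3-year look as the safety safeguard.

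**Cost.** A protocol amendment, and one or two DMC meetings brought forward. The real limit is information. If the 15% restenosis rate in Sample size is taken as a 3-year figure at a constant rate (my assumption), about 15%/12 = 1.25% would have restenosis by 3 months. That is about 0.4 events per arm with 69 patients (34.5 × 0.0125) and 0.9 with 138 (69 × 0.0125). A test on restenosis would show almost nothing this early, so these looks must rest mainly on adverse events.
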